## Abstract

**Introduction:**

Statin therapy is known to reduce subsequent cardiovascular events in patients who had an ischaemic stroke and transient ischaemic attack (TIA). However, its effectiveness and safety in frail older adults with a recent stroke or TIA are uncertain, leading to variations in clinical practice. ‘StAtins in Frail oldEr patients with ischemic Stroke or Transient ischemic attack–the Randomized Controlled Trial’ (SAFEST-RCT) aims to investigate the effectiveness of initiating versus not initiating statin therapy in this vulnerable population, to optimise secondary prevention strategies.

**Methods and analysis:**

This multicentre, prospective, randomised, open-label study aims to enrol 612 frail adults ≥70 years with a recent acute ischaemic stroke or TIA across 22 Dutch hospitals. The study compares prescribing versus not prescribing statins in terms of health-related quality of life, major adverse cardiovascular event-free survival and societal costs over a 2-year follow-up period.

**Ethics and dissemination:**

The SAFEST-RCT protocol was approved by the Ethics Committee of Amsterdam UMC. It complies with the Declaration of Helsinki and is classified as a healthcare evaluation. Recruitment began in March 2025. Results will be published in open access journals, presented at conferences, shared via the Dutch Brain Injury Association and integrated into national guidelines to support implementation in routine care.

**Trial registration number:**

NCT06785727.

WHAT IS ALREADY KNOWN ON THIS TOPICStatins reduce cardiovascular events after ischaemic stroke or transient ischaemic attack (TIA), but evidence for their use in frail older adults is lacking due to their under-representation in trials, resulting in clinical uncertainty.WHAT THIS STUDY ADDSThis trial evaluates the effectiveness of prescribing versus not prescribing statins on quality of life and cardiovascular outcomes in frail older patients who had a stroke and TIA.HOW THIS STUDY MIGHT AFFECT RESEARCH, PRACTICE OR POLICYFindings will provide essential guidance for clinical decision-making in this vulnerable and understudied population.

## Introduction

### Background

 Age is a major risk factor for ischaemic stroke and transient ischaemic attack (TIA).^1^ With the global population ageing rapidly, the global incidence of these conditions is expected to rise by 81% between 2021 and 2050.^2^ Ischaemic stroke is a leading cause of disability and generates significant economic burden.^1 3^ As individuals who have suffered an ischaemic stroke or TIA are at increased risk for subsequent cardiovascular events,^1 4 5^ secondary prevention is deemed essential.^6^

Statins are a key component of secondary prevention and have been proven effective in middle-aged patients who had a stroke and TIA.^6 7^ Due to their higher baseline risk, the absolute benefit of statins is expected to be greater in older individuals. However, due to the under-representation of frail older patients in statin trials, there is limited evidence regarding the effectiveness and safety of statins in this population.^8^

A recent meta-analysis of 28 randomised controlled trials (RCTs), including the Pravastatin in elderly individuals at risk of vascular disaese (PROSPER) trial, the Heart Protection Study (HPS) and the Justification for the use of statin in prevention: an intervention trial evaluating rosuvastatin (JUPITER) trial, showed that statins used for secondary prevention lowered the annual incidence of major adverse cardiovascular events (MACE) from 5.8% to 4.8% in people aged 70–75 years, and from 6.8% to 6.0% in people over 75 years.^7^ However, the 17 trials that included older participants excluded individuals with conditions such as multimorbidity, cognitive impairment, life expectancy of less than 5 years, severe heart failure, chronic liver or kidney disease or uncontrolled diabetes. This likely restricted the inclusion of frail individuals. Given that frailty affects approximately 20% of community-dwelling adults aged over 70, 31% of those over 80 and 51% of those over 90 years,^9^ the exclusion of this subgroup creates a substantial evidence gap.

While it might be tempting to extrapolate the benefits of statin therapy from fit to frail older patients, substantial differences between these populations must be acknowledged. In frail older adults, it is essential to consider time to benefit.^10^ Both frailty and a history of ischaemic stroke or TIA independently reduce life expectancy in older individuals, and their combination further worsens prognosis.^11^,^13^ Although lipid lowering and plaque stabilisation can occur within months after starting statin therapy,^14^ a full reduction in cardiovascular events typically requires years.^15^ The results of a meta-analysis indicated that 2.5 years of statin therapy are needed to prevent one MACE per 100 adults aged 50–75.^15^ Consequently, frail older stroke survivors with limited life expectancy may not live long enough to fully benefit from statin therapy.

Frailty also increases the risk of adverse effects.^16^ Statins can cause muscle pain, myopathy, elevated liver enzymes and diabetes mellitus.^17 18^ No significant association has been found between statin use and adverse cognitive effects.^19^ However, the under-representation of frail older individuals in clinical trials may have led to an underestimation of the full spectrum of statin-related risks. Age-related changes in pharmacokinetics and pharmacodynamics, comorbidities and polypharmacy further elevate the risk of adverse effects and drug interactions in this population.^20^,^24^ Even mild adverse effects like myopathy can severely impact mobility, increase fall risk and reduce quality of life (QoL) in frail individuals.^25^ While older adults often prioritise health-related quality of life (HRQoL), daily functioning and independence over mortality,^26 27^ statin trials typically focus primarily on outcomes such as recurrence of cardiovascular events and mortality.^28^ A recent systematic review and meta-analysis by our group found no conclusive evidence that statin use improves QoL or functional status in older patients following ischaemic stroke or TIA.^29^ Furthermore, an RCT involving individuals with a life expectancy of less than 1 year found that discontinuation of statin therapy was associated with improvements in QoL.^30^

Stroke-related healthcare costs are substantial.^3^ Statin therapy as secondary prevention is generally considered cost-effective.^31^ However, in frail older patients with limited life expectancy, higher risk of adverse effects and potentially diminished QoL benefits, cost-effectiveness remains uncertain.

### Objectives

The lack of strong evidence for statin use for secondary prevention in frail older adults has led to uncertainty in clinical guidelines. The 2018 American College of Cardiology guideline recommends statin therapy for patients over 75 who had a stroke, after evaluating recurrence risk, adverse effects, drug interactions and frailty.^32^ Similarly, the 2021 European Society of Cardiology guideline emphasises the need to consider frailty, polypharmacy and muscle symptoms in older adults.^33^ However, neither provides specific guidance for the frail population, contributing to uncertainty and variations in clinical practice.^8^

The StAtins in Frail oldEr patients with ischemic Stroke or Transient ischemic attack–the Randomized Controlled Trial (SAFEST-RCT) aims to clarify these uncertainties by comparing the effects of starting versus withholding statins on HRQoL and MACE-free survival in frail older patients during the first 2 years after ischaemic stroke or TIA.

## Methods

### Study design

This multicentre, prospective, randomised, open-label trial with blinded outcome evaluation is being performed across 22 Dutch hospitals (online supplemental appendix 1: participating study sites). The protocol follows the Standard Protocol Items: Recommendations for Interventional Trials 2013 guideline.^34^

### Participants

Eligible participants must meet the following criteria: (1) a neurologist-confirmed ischaemic stroke or TIA within 6 weeks prior to inclusion; (2) an age ≥70 at the time of the event; (3) not receiving statins at the time of the event; and (4) frailty, defined as a Clinical Frailty Scale (CFS) score of 4–7 pre-event and/or 6–7 post-event.^35^ The CFS evaluates domains such as daily and cognitive functioning and comorbidity, generating a frailty score from 1 (very fit) to 9 (terminally ill); scores ≥4 usually indicate frailty due to increased susceptibility to adverse outcomes, including reduced life expectancy.^35 36^

Exclusion criteria consist of: (1) a history of serious statin-related adverse reactions or contraindications (eg, severe liver disease); (2) very severe frailty (CFS ≥8); (3) inability to communicate in Dutch; (4) inability to respond to questions, independently or with the assistance of a proxy; (5) inability or unwillingness to provide written informed consent, independently or with the assistance of a proxy; (6) extremely high cardiovascular risk, defined as ≥1 cardiovascular event in the year before the index event; and (7) non-atherosclerotic stroke or TIA with no vascular risk factors.

Verbal consent to be contacted by an investigator is obtained by the treating neurologist. The local investigator then provides detailed study information (online supplemental appendix 2: participant information form) and obtains written informed consent, allowing at least 48 hours for consideration. Additional consent is sought for ancillary and follow-up studies. Randomisation is performed using Castor EDC (v.2025.1.2.0). Block (2:4) randomisation is used, stratified by hospital and type of event (ie, TIA or ischaemic stroke), with a 1:1 allocation ratio.

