### Intervention

Allocation details are communicated to the treating neurologist. In the intervention group, a statin is newly prescribed. Low-density lipoprotein (LDL) target levels are <1.8 mmol/L (<70 mg/dL) after atherosclerotic ischaemic stroke or TIA, and <2.5 mmol/L (<100 mg/dL) after non-atherosclerotic ischaemic stroke or TIA in the presence of vascular risk factors, based on the Dutch Stroke guideline (May 2019).^37^ Statin type and dose are at the neurologist’s discretion, and the statin is collected by the participants at their own pharmacy. In the control group, no statin is prescribed, in line with the Dutch Cardiovascular Risk Management guideline (March 2019), which recommends considering not to start statin treatment in frail older patients, especially when an adverse effect is being suspected or when life expectancy is reduced.^38^

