### Data collection and outcomes

The study evaluates the impact of statin prescription on two primary outcomes:

*HRQoL*, measured by the Patient-Reported Outcomes Measurement Information System 10-Question Short Form (PROMIS-10), which includes subscales for mental health and physical health.^39 40^*Three-point MACE-free survival*, defined as survival without any of the following MACEs: cardiovascular death, non-fatal myocardial infarction or non-fatal stroke. MACE events are self-reported by participants or reported by a proxy using a calendar returned every 3 months and are verified annually with treating physicians.

Secondary outcomes include functional outcome assessed using the modified Rankin Scale^41^; falling using a falls calendar; cognitive functioning using the Montreal Cognitive Assessment (MoCA)^42^ or the Telephone version of MoCA^43^; quality-adjusted life-years (QALYs) based on the EuroQol 5-Dimension 5-Level (EQ-5D-5L)^44^ questionnaire; and societal costs using The Older Persons and Informal Caregivers Survey–Minimum DataSet (TOPICS-MDS).^45^

At baseline, demographics, medication use and recent clinical metrics and laboratory values are extracted from the electronic patient record by local investigators. Furthermore, the PROMIS-10, MoCA, EQ-5D-5L, TOPICS-MDS and CFS are assessed. Follow-up continues for 24 months, with an optional 1-year extension for early enrollees. Assessment frequencies vary by outcome measure (figure 1). Participants, caregivers and local investigators are not blinded. However, all follow-up is conducted by investigators from the central research team who are blinded to treatment allocation.

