## Ethics and dissemination

The protocol was registered on ClinicalTrials.gov (NCT06785727) on 19 December 2025. The study complies with the Declaration of Helsinki and is classified as a healthcare evaluation, comparing two standard-of-care strategies recommended in Dutch guidelines. Given the study’s low-risk nature, a Data Safety Monitoring Board and subject insurance were not required. All centres are covered by institutional liability insurance in accordance with the Dutch Medical Research Involving Human Subjects Act. Adverse events are recorded in Castor; serious adverse events are reported to the central research team and included in annual safety reporting.

Recruitment began in March 2025; the last patient is expected to be included in January 2027, with data collection concluding by January 2029. Data are handled in accordance with the General Data Protection Regulation (European Union) 2016/679. Independent monitoring is performed by the Amsterdam UMC Clinical Monitoring Center, following the study’s monitoring plan (online supplemental appendix 3: monitoring plan). Baseline data are extracted from hospital records and questionnaires; follow-up data come from general practitioners and participant questionnaires. Source documents are securely stored at study sites, while follow-up data are centrally managed at Amsterdam UMC. All study data will be archived for 25 years. Deidentified data will be made available on reasonable request, in line with ethical approvals and data protection regulations. Further details on data management, storage and governance are available in online supplemental appendix 4: data management plan.

The results of this trial will be submitted for publication in peer-reviewed open access journals and presented at national and international conferences. In collaboration with the Dutch Brain Injury Association, findings will also be disseminated through patient networks and the association’s website to reach a broader public. This study will provide valuable insights and have direct implications for clinical practice. Results will be integrated into Dutch national guidelines, facilitating implementation in routine care.

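### Blocks of 2 and 4 within 44 hospital-by-event strata, with past allocations known to the recruiting staff, make the next allocation materially guessable and leave enrolment open to selection bias

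*Protocol article*

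**What the plan says.** Under Participants, the protocol article says "Block (2:4) randomisation is used, stratified by hospital and type of event", "with a 1:1 allocation ratio". It does not explain the 2:4 notation; the natural reading is block sizes of 2 and 4. The list sits in an electronic system: "Randomisation is performed using Castor EDC (v.2025.1.2.0". The trial "is being performed across 22 Dutch hospitals" (Study design).

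The same section gives entry to two roles. The treating neurologist obtains verbal agreement to be contacted. After that, "The local investigator then provides detailed study information" and takes written consent.

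Both roles learn earlier allocations. Under Intervention, "Allocation details are communicated to the treating neurologist". Under Data collection and outcomes, "Participants, caregivers and local investigators are not blinded"; only the central follow-up team is blinded.

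Under Ethics and dissemination, "Recruitment began in March 2025; the last patient is expected to be included in January 2027". The article therefore prints the block sizes of a trial whose recruitment is planned to run to January 2027. It says nothing about predictability or about withholding the sizes from recruiters.

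**The concern.** In an open-label trial a central system hides the list, but it does not hide what the list has already produced. When blocks are short and each stratum belongs to one hospital, the staff there can see which arm is behind and infer which is likely to come next. A recruiter with a view on statins in frail patients can then, even without intending it, approach one patient now and another later, or present the trial differently.

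Prior views are plausible here, because the article itself describes variation in practice and guideline uncertainty. Eligible patients also differ widely in prognosis: the Clinical Frailty Scale (CFS) runs from 4 to 7 before the event, and the sample-size section expects only 52% two-year survival in the control group. If frailty differed between arms because of selection, MACE-free survival would be affected. So would health-related quality of life, in which deaths are scored 0. Blinded follow-up acts after enrolment and cannot repair this.

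**Working it through.** The article gives no predictability figure, so there is none to reproduce. The sample size of 612 is used only as an input.

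**Inputs.** From the article: 612 patients, 22 hospitals, two event types, 1:1 allocation, block sizes 2 and 4, recruitment from March 2025 to January 2027 (about 22 months). Assumed: sizes mixed at random with equal weights, and a recruiter who knows every earlier allocation in the stratum and the set of sizes, but not the size of the current block.

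**Step 1: size and pace of the strata.** 22 × 2 = 44 strata, and 612 / 44 = 13.9 patients each on average. 612 / (22 hospitals × 22 months) = 1.3 patients per hospital per month, spread over two strata. A history that short is easy to remember.

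**Step 2: the second patient of a block.** Let *w* be the share of blocks of size 2. After the first patient of a block, the opposite arm follows with probability *w* × 1 + (1 − *w*) × 2/3.
- *w* = 1/2: 0.50 + 0.33 = 0.83
- *w* = 1/3: 0.33 + 0.44 = 0.78
- *w* = 1/4: 0.25 + 0.50 = 0.75

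**Step 3: exact bounds.**
- All blocks of 2: every second allocation is certain (50%), and the best guess is right (0.5 + 1)/2 = 75.0% of the time.
- All blocks of 4: certain (1/3 + 1)/4 = 33.3%; best guess right (1/2 + 2/3 + 2/3 + 1)/4 = 70.8%.
- Mixed 2 and 4 with each block's size known: certain (2 × 0.500 + 4 × 0.333)/6 = 38.9%; best guess right (2 × 0.750 + 4 × 0.708)/6 = 72.2%.

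**Step 4: mixed sizes, current size unknown.** The probability of the next allocation was updated by Bayes' rule over the possible block states, in simulated strata of 14.

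| Blocks | Best guess right | At least 80% confident | At least 90% confident | Certain |
|---|---|---|---|---|
| 2 and 4, equal weights | 72% | 55% | 19% | 10% |
| 2 and 4, weights 1:2 | – | 44% | – | – |
| 2 and 4, weights 1:3 | – | 36% | – | – |
| 4, 6 and 8, equal weights | 67% | 18% | 3% | 2.5% |

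With equal weights, guesses made at 80% confidence or more were right 89% of the time. Stratum size matters little. Over strata of 4 to 100 patients the best guess is right 70.8% to 72.1% of the time, and 8.5% to 11.0% of allocations are certain. The 80% share is 54.3% in strata of 6 and 55.3% in strata of 28.

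**Step 5: how far the threshold drives the result.** For 2 and 4 with equal weights, the share is 55% at 80% confidence, 44% at 85% and 19% at 90%. The 80% cut lies just below the 0.83 of Step 2 and so captures those allocations. With weights 1:2 or 1:3 the Step 2 figure drops to 0.78 or 0.75, below the cut, and the share falls. At a 70% cut the shares are 55% for 2 and 4, against 52% for 4, 6 and 8.

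**The case against.** A reader might infer that more than half of allocations are known in advance, or that the next one is often nearly certain. The documents do not support either. About 10% are certain under the mixed reading, 39% if the size of each block were known, and exactly 50% even if every block had size 2. Fewer than one in five reach 90% confidence. The 55% figure belongs to one threshold and to equal weights, which the article does not state; with blocks of 4 more common it is below half. Nor is guessing more than half correctly informative by itself, since chance gives 50%.

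A reader might also infer that selection has taken place. Nothing shows that. The list is held in Castor and nothing suggests recruiters can see it. The consent period of at least 48 hours is time for the patient to consider, and the article does not present it as anything else. Recruitment is split between neurologist and local investigator, and several people per hospital would each know only part of the history.

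The gain from larger blocks also depends on the measure. On the threshold-free one it is modest: 72% to 67% removes about 5 of the 22 points above chance.

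All of this limits the size of the claim. What stands is that a best guess beats chance by more than 20 points under every 2-and-4 reading in Step 3, that the article informs both recruiting roles of earlier allocations, and that central allocation does not prevent the inference. This is a stated design choice, not a detail left to a fuller document.

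**Conclusion.** The point holds as a design weakness. Short blocks within 44 small hospital-level strata, with allocations known to those who approach and consent patients, leave enrolment materially guessable: about 72% against 50% by chance, about 10% certain, and about 55% at 80% confidence or more (36% to 44% if blocks of 4 are two to three times as common). These figures assume randomly mixed sizes, equal weights except where stated, and full tracking of the stratum by one recruiter; several recruiters would lower them. The harm is possible and has not been shown, and no size of bias on either primary outcome can be derived from the article. Because the remedy is cheap and recruitment is planned to January 2027, the change should be made.

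**What to change.** **Further randomisations.** Load a Castor list with larger, randomly varying blocks, for example 4, 6 and 8. Keep the sizes out of site documents and leave the strata unchanged. Under the same assumptions, best guesses fall to about 67%, allocations predictable with at least 80% confidence to 18%, and certain ones to about 2.5%. Confident prediction falls about threefold and average guessing only a little.

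**Patients already randomised.** From the actual list, compute each patient's predicted probability of statin allocation given the earlier allocations in the stratum. Examine baseline CFS and age against it, within strata. Without selection there should be no relation. A relation would be a warning sign; its absence would not exclude bias.

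**Cost.** A short amendment and a new list. Within-stratum imbalance can reach 4 instead of 2, and the standard deviation of the overall arm difference rises from about 4.5 to about 7 patients in 612, which is small. The Primary outcomes section names adjustment for event type only, so the analysis should account for hospital as well; that addition belongs in the same amendment.

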### Intervention

Allocation details are communicated to the treating neurologist. In the intervention group, a statin is newly prescribed. Low-density lipoprotein (LDL) target levels are <1.8 mmol/L (<70 mg/dL) after atherosclerotic ischaemic stroke or TIA, and <2.5 mmol/L (<100 mg/dL) after non-atherosclerotic ischaemic stroke or TIA in the presence of vascular risk factors, based on the Dutch Stroke guideline (May 2019).^37^ Statin type and dose are at the neurologist’s discretion, and the statin is collected by the participants at their own pharmacy. In the control group, no statin is prescribed, in line with the Dutch Cardiovascular Risk Management guideline (March 2019), which recommends considering not to start statin treatment in frail older patients, especially when an adverse effect is being suspected or when life expectancy is reduced.^38^

